## 147 **9. Analysis plan**

148 To compare sample characteristics between arms we will use t-tests or Wilcoxon rank-sum tests (F-tests or  
149 Kruskal-Wallis test) for continuous variables and Pearson chi square tests or Fisher's exact tests for categorical  
150 variables. In our primary analyses, we will compare rates of opioid disposal (baseline vs. 6-week study period).  
151 In the secondary analysis we will compare self-reported pain intensity, ability to manage pain, and opioid use.  
152 All hypothesis tests will be two-sided using a two-sided alpha of 0.025 as our threshold for statistical  
153 significance. We will use Stata and/or SAS to analyze the data.

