## 3. Aims

### *3.1 Primary outcome*

The primary outcome variable is rate of self-reported opioid disposal.

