### *5.4 Accrual*

We estimate that a sample size of 250 participants (125 per arm) will provide at least 80% power using a conservative Bonferroni adjustment of the Type I error rate with a 2-sided  $\alpha$  of 0.025 to detect a 20% change in disposal rates. Preliminary data suggest a baseline rate of 25%.

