### *8.2 Procedures*

After providing informed consent, participants will be sent messaging on post-operative days 4, 7, 14, 21, and 28. At each time point, patients are asked to self-report pain intensity (scale 0-10, 10 being severe), ability to manage pain (scale 0-10, 10 being very able to manage), and use of non-opioid and opioid analgesics. Patients who are using opioid analgesics are asked to report quantity used, projection of future use for acute pain. Patients reporting no further use are asked about disposal (Yes or No).

Patients will be mailed opioid disposal packets, DispoRx, which are small chemical polymers which individuals can pour directly into a pill bottle. The individual shakes the bottle and the medication is deactivated, rendered unusable and can be placed safely in the trash. We will mail these packets to individuals within the first 7 days for Orthopedic and Urology and timed for 21 days for Neurosurgery.

145 Participants will be randomly assigned at the individual level to receive a disposal packet. Participants  
146 randomized to the control arm will receive no other interventions.

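### The primary disposal outcome has no time point or rule for combining five contacts, and the only stated contrast is neither between the arms nor tied to a post-operative day, so the primary test is left open to choice

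*Supplement*

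**What the plan says.** Section 3.1 of the protocol reads: "The primary outcome variable is rate of self-reported opioid disposal". It gives no day, window or denominator.

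Section 8.2 says "participants will be sent messaging on post-operative days 4, 7, 14, 21, and 28". It has the questions put at each of these contacts and restricts the disposal question to patients who report no further use. It times kit mailing within the first 7 days for orthopedics and urology, and "timed for 21 days for Neurosurgery". Section 5.1 has the kit mailed once the participant responds and consents on day four, with no exception by service.

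Section 9 says "In our primary analyses, we will compare rates of opioid disposal", followed by a bracket that sets baseline against the six-week study period. It adds: "All hypothesis tests will be two-sided using a two-sided alpha of 0.025 as our threshold for statistical" significance. Section 5.4 calls the 0.025 a "conservative Bonferroni adjustment of the Type I error rate" but does not name the tests it covers. Its 25% baseline rate has no day attached.

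In the texting script, the disposal question (Q9) is reached only after a No to Q8 on planned further use. Re-texting a week later is written only after a Yes to Q8. A No to Q5 (opioid taken) or to Q7 (pills remaining) skips Q9.

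**The concern.** A two-arm randomized trial needs one stated comparison of the arms on a defined quantity. Here the outcome section names no day. The analysis section names a comparison of periods that does not use the randomization, and the sample-size section does not fill the gap. Six weeks is the calendar length of the study (sections 5.1 and 5.2), whereas a participant's messages end on day 28. "Baseline" could mean the day-4 answer or the preliminary 25% rate.

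An analyst who wants to compare the arms must therefore choose the day or summary, and nothing written stops that choice being made after the data are seen. The choice also changes what is estimated. Day 4 cannot show a kit effect in anyone. On section 8.2's timing, days 7 and 14 cannot show one in neurosurgery, and day 21 hardly can. Two things are at stake: the error rate of the primary claim, and whether the measured quantity reflects exposure to the kit.

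**Working it through.** **1. The plan's own figure.** Section 5.4 states: "We estimate that a sample size of 250 participants (125 per arm) will provide at least 80% power", at a two-sided alpha "of 0.025 to detect a 20% change in disposal rates", from a 25% baseline. Read as 25% vs 45%, with n = 125 per arm and critical value 2.2414:

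- Pooled rate 0.35; null standard error = √(0.35 × 0.65 × 2/125) = 0.06033.
- Alternative standard error = √(0.25 × 0.75/125 + 0.45 × 0.55/125) = 0.05899.
- Power = Φ[(0.20 − 2.2414 × 0.06033)/0.05899] = Φ(1.098) = 86.4%.

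This meets the stated 80%, for which 107 per arm would be enough. A relative change (25% to 30%) would give 8.7%, so absolute points are evidently meant. The calculation is for one test of one pair of rates.

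**2. Does any section fix the primary test?**

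| Section | Day or window | Contrast |
|---|---|---|
| 3.1 | none | none |
| 5.4 | none for the 25% rate | a change in rates, 125 per arm |
| 8.2 | five contacts, no primary one | none |
| 9 | six-week study period | baseline vs that period, not between arms |

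None does.

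**3. Error rate if several days were tested and any one sufficed.** No true effect, each test two-sided at 0.025.

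- Independent days: 1 − 0.975⁵ = 11.9% for five; 1 − 0.975⁴ = 9.6% for four.
- Equicorrelated normal test statistics, P(at least one |Z| > 2.2414):

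| Assumed correlation | Five days | Four days (without day 4) |
|---|---|---|
| 0.5 | 9.8% | 8.2% |
| 0.7 | 8.0% | 7.0% |
| 0.9 | 5.4% | 4.9% |

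- Cumulative disposal by day, simulated at 125 per arm under four assumed time courses reaching 25% to 50% by day 28: 5.8% to 8.5% for five days, 5.0% to 7.1% for four.
- Different patients answering on each day, as the script's re-texting rule may imply: 11.6% to 11.8% for five days.
- A false finding in favour of the kit is about half of each equicorrelated figure: 2.7% to 4.9% for five days at correlation 0.9 to 0.5.

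The correlations and time courses are assumptions; the documents give neither.

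**4. The alternatives.** One pre-specified test has an error rate of 2.5% and power of 86.4%. Splitting 0.025 over five days (0.005 each) gives 69.8% power per day, and 80% power would need 150 per arm.

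**5. Denominator.** Suppose 25% vs 45% applies only to participants who are asked about disposal, and those not asked count as not having disposed. The rates then shrink by the share asked, and the formula in step 1 gives:

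| Assumed share asked | Rates compared | Power |
|---|---|---|
| 90% | 22.5% vs 40.5% | 80% |
| 80% | 20% vs 36% | 72% |
| 60% | 15% vs 27% | 54% |

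**The case against.** The strongest objection is that by-day testing is nowhere in the plan. No section says that disposal will be tested on each day or that one significant day is enough. Section 9's plural wording proves nothing, since comparing two groups always involves two rates. A reader might infer from the five contacts and the uniform 0.025 that the primary claim carries a 5% to 10% error rate. The documents do not support that: a single summary keeps 2.5%, and the higher figures apply only if several days are examined and any one may carry the claim. This part of the objection stands.

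It is also fair that section 9 does name a contrast. But that contrast compares periods rather than arms and gives no day, so it does not settle the primary test and is itself a fault.

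The script's logic may mean that each patient answers the disposal question about once, which would suit a single pooled proportion. Section 8.2 points the other way. The conflict decides how far the days overlap, and therefore which error rate would apply.

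Finally, the argument about unexposed neurosurgery patients rests on section 8.2, and section 5.1 gives no such exception. A reader might also infer a definite loss of power, or opposite conclusions, from using an earlier day. The documents give neither the neurosurgery share nor a time course for disposal, so no such loss can be put in figures.

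**Conclusion.** The point holds in conditional form. What is certain from the text is that the primary outcome has no time point and no rule for combining contacts, and that the stated contrast neither compares the arms nor fixes a post-operative day. Followed as written, section 9 does not yield a sound primary test of the kit.

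The inflation of the error rate is a risk that the plan leaves open, not a property of a stated procedure. It could reach two to four times 2.5% for five days at assumed correlations of 0.9 to 0.5, and somewhat less for the four days that can follow a kit. The Bonferroni step does not remove that risk: 0.025 is apparently 0.05/2 for two unnamed tests, and it cannot also cover five days. The sponsor should correct this before analysis.

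**What to change.** - In sections 3.1 and 9, replace the baseline-versus-study-period bracket with one contrast, tested once at the stated alpha: the proportion reporting disposal at any contact up to and including day 28, kit arm vs control arm. Day 28 is already scheduled and is the only contact after section 8.2's neurosurgery kit timing.
- Report rates by days 7, 14 and 21 as estimates with confidence intervals and no significance claim. Do not test day 4.
- State the denominator, and how participants who do not respond or are never asked the disposal question are counted.
- Reconcile section 8.2 (messages to all on five days) with the script (re-texting written only after a Yes to Q8), and sections 5.1 and 8.2 on kit timing.

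This takes a few sentences and needs no new data or patients. There are two costs. A difference on an earlier day can no longer be claimed as confirmatory. With all randomized participants as the denominator, power may fall below 86%, as in step 5 of the working, so the sponsor should recheck the sample size against the denominator chosen.

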## **5. Study design**

### *5.1 Design*

This is a two-arm, randomized, controlled trial. The study will be conducted using an automated, remote text messaging platform (Way to Health) which delivers text messaging following orthopedic, neurosurgical, and urology procedures at the University of Pennsylvania.

The study team will identify potential participants from the electronic health record at the University of Pennsylvania Health System using Penn Data Store and Clarity, an EPIC reporting database. Patients undergoing a procedure in neurosurgery, orthopedics, or urology and who are prescribed an acute opioid will receive a text message four days following their discharge. This established system obtains remote, text-messaged based consent on post-operative day four. For those consenting, patients are queried on self-reported pain intensity, ability to manage pain, use of non-opioid analgesics, use of opioid analgesics, and opioid disposal. Once a participant responds and consents on day four, the participant will be mailed an opioid disposal kit which includes an informational sheet and the chemical packet (DispoRx).

Participants will be randomly assigned to intervention or control according to calendar week of surgery in alternating weeks over a 6-week period. Participants randomized to the control arm will receive no other interventions.

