**Q4:**

*"We just have a few more questions. [line break] Have you taken any of the following medications for your pain since your procedure (Acetaminophen, Aspirin, Ibuprofen, or Naproxen)? [Y for yes or N for no]. "*

326 LOGIC:

327 ○ If response = Y, N, yes, or no → Proceed to **Q5**

328 ○ If response ≠ Y, N, yes or no → REPLY "I'm sorry. We don't understand. Please text back Y or N."

329

330 **Q5:**

331 *"Thanks, this information helps guide our practice. It looks like you were also prescribed [opioid\_RX] for your*

332 *pain. [line break]Have you taken this medication? [Y for yes or N for no]."*

333

334 LOGIC:

335 ○ If response = Y or yes → Proceed to **Q6**

336 ○ If response = N or no → Proceed to **Q10**

337 ○ If response ≠ Y, N, yes or no → REPLY "I'm sorry. We don't understand. Please text back Y or N."

338

339 **Q6:**

340 *"Can you estimate how many pills of [opioid\_RX] you have taken since your procedure? Please text back a*

341 *number"*

342 LOGIC:

343 ○ If response = Number → Proceed to **Q7**

344 ○ If response ≠ Number → REPLY "I'm sorry. We don't understand. Please text back a number."

345

346

347 **Q7:** *"Do you have any of these pills remaining? [Y/N]"*

348 LOGIC:

349 ○ If response = Y, yes → Proceed to **Q8**

350 ○ If response = N, no Proceed to **Q10**

351 ○ If response ≠ Y, N, yes or no → REPLY: *"I'm sorry. We don't understand. Please text back Y or N."*

352

353

354 **Q8:** *"Do you plan to continue taking [opioid\_RX] to control your pain? [Y/N]"*

355 LOGIC:

356 ○ If response = Y or yes → REPLY: *"Thanks so much for your feedback! We'll check back with you in a few*

357 *days. If you have any questions or concerns about your care or health please contact your surgical team.*

358 *Have a nice day!"*

359

360 ---This patient will be texted in 1 week---

361

362  
363  
364  
365  
366  
367  
368  
369  
370  
371  
372  
373  
374  
375  
376  
377  
378  
379  
380  
381  
382  
383  
384  
385

- If response = N or no → **Move to Q9**
- If response ≠ Y, N, yes or no → REPLY: *"I'm sorry. We don't understand. Please text back Y or N."*

**Q9:** "Have you disposed of your unused %opioid% medication? [Y/N]"

LOGIC:

- If response = Y or Yes → That's great to hear. It's important to dispose of your unused medication. Just one more question for you: [line break] *"How many days did it take for your pain to improve after your procedure? Please text back a number."*

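### Section 9 plans no adjustment of the primary disposal comparison for day-4 opioid-use status, which is already collected before any kit is mailed and could add precision at almost no cost

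*Supplement*

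**What the plan says.** - **Primary analysis (section 9).** The plan states "In our primary analyses, we will compare rates of opioid disposal", followed by a parenthesis that sets baseline against the six-week study period. No test, model, covariate, stratum or denominator is named. The threshold is set by "using a two-sided alpha of 0.025 as our threshold".
- **Timing (section 5.1).** "Once a participant responds and consents on day four, the participant will be mailed an opioid disposal kit". The day-4 exchange, which asks about pain, opioid use and disposal, therefore precedes mailing. Section 8.1 adds that the existing questions and their timing stay as they are.
- **Who is asked (section 8.2).** "Patients reporting no further use are asked about disposal (Yes or No"). Messages go out on days 4, 7, 14, 21 and 28.
- **Routing (text-message script).** The disposal question, script Q9, is reached only if the opioid was taken (Q5 yes), pills remain (Q7 yes) and no further use is planned (Q8 no). Q5 no and Q7 no both go to Q10 and skip Q9. Q8 yes leads to another text a week later.
- **Sample size (section 5.4).** "a sample size of 250 participants (125 per arm") "will provide at least 80% power" "to detect a 20% change in disposal rates", from a baseline rate of 25%.

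**The concern.** Whether and when a participant can report disposal depends on answers that the trial already holds before the kit is sent. If day-4 status predicts reported disposal, an analysis that ignores it has a wider interval than the same data allow. It also leaves chance imbalance uncorrected. If half the patients plan to continue on day 4, the arm difference in that share has standard deviation √(2 × 0.25/125) = 0.063, so a gap above 10 percentage points arises in about 11% of trials. Adjustment chosen after such a gap is seen is open to challenge; prespecified adjustment is not.

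Full accrual leaves some margin over 80% power, but section 5.4 states no allowance for attrition and follow-up runs to day 28.

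**Working it through.** **Inputs.** From section 5.4: control rate p0 = 0.25, n = 125 per arm, two-sided alpha 0.025 (z = 2.2414). The 20% change is read as percentage points, so p1 = 0.45. A relative reading (25% vs 30%) would give 8.7% power, so the absolute reading must be meant. The variance explained by the day-4 answers, R², is not in the documents and is varied.

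**1. The plan's figure.** Power = Φ[(|p1 − p0| − z·SE0)/SE1], with SE0 = √(2 × 0.35 × 0.65/125) = 0.0603 and SE1 = √((0.25 × 0.75 + 0.45 × 0.55)/125) = 0.0590. This gives Φ[(0.20 − 0.1352)/0.0590] = Φ(1.098) = 86.4%, or 83.2% with continuity correction. The claim of at least 80% reproduces; 107 per arm would suffice without continuity correction.

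**2. Adjustment with assumed R².** Both standard errors are multiplied by √(1 − R²). At R² = 0.10, for example: Φ[(0.20 − 0.1283)/0.0560] = 90.0%.

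| R² | 125 per arm | 100 evaluable per arm (assumed) |
|---|---|---|
| 0 | 86.4% | 77.0% |
| 0.05 | 88.2% | 79.4% |
| 0.10 | 90.0% | 81.7% |
| 0.15 | 91.7% | 84.1% |
| 0.20 | 93.3% | 86.4% |
| 0.25 | 94.8% | 88.7% |

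**3. A status that fully gates reported disposal.** If only a share q of patients can ever report disposal, each arm's within-stratum variance is p(1 − p/q). At q = 0.64 these sum to 0.25 × 0.609 + 0.45 × 0.297 = 0.286, against 0.435 unadjusted, so R² = 0.34 and power is 96.6%. At q = 0.75 power is 93.0%; at q = 0.90 it is 88.7%. The values of q are assumptions.

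**4. Simulation.** 125 per arm, half of patients planning to continue on day 4, overall rates 25% vs 45%, pooled z-test against a Cochran-Mantel-Haenszel test on a binary day-4 status (20,000 or 40,000 runs). Rates are given as not continuing/continuing.

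| Control | Kit | Unadjusted | Stratified |
|---|---|---|---|
| 40/10 | 60/30 | 86.5% | 90.3% |
| 45/5 | 70/20 | 86.5% | 94.0% |
| 25/25 (no association) | 45/45 | 87.0% | 86.7% |
| 40/10 (effect only in continuing) | 40/50 | 86.7% | 86.9% |
| 35/15 (effect only in continuing) | 35/55 | 86.8% | 86.5% |
| 45/5 (effect only in continuing) | 45/45 | 86.5% | 88.1% |

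Repeat runs put the effect-only-in-continuing cases between about 0.4 points lost and 1.5 to 2 points gained. With a four-level status and the branches that skip Q9 kept in the denominator, the gain was about 4 to 10 points.

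**The case against.** The strongest case against runs as follows.

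- **An unadjusted comparison of two proportions is valid in a randomized trial, and it already meets the stated power.** This stands. No target in section 5.4 is missed at full accrual.
- **The gain is assumed.** This also stands. Nothing in the documents links day-4 answers to later disposal.
- **The gain may nearly vanish.** A patient not planning to continue is asked about disposal in the same day-4 exchange, before a kit can arrive, and the script shows a repeat text only after a plan to continue. On that reading the kit can change recorded disposal only among continuing patients, and adjustment gains from about nil to 2 points. Section 8.2 can also be read as asking everyone again through day 28, so neither reading is settled.
- **The denominator is undefined.** If only patients who reach Q9 are counted, the gate is already built in and adjustment gains less.
- **Before the kit is not necessarily before assignment.** Section 5.1 assigns by alternating calendar weeks of surgery, section 8.2 at the individual level. Under the former, day-4 answers follow assignment and are suitable covariates only if unaffected by knowledge of the arm. Power figures for independent patients may then not apply either.

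A reader might infer that day-4 answers decide whether a patient can dispose at all. The documents do not support this. Only having no pills left rules disposal out. A plan to continue is asked about again, and a patient who took none may hold every tablet but is routed past the question, which is a gap in measurement. That the analysis is unadjusted is likewise inferred from silence: section 9 names no test.

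**Conclusion.** The point holds as an efficiency improvement, between optional and recommended. Section 9 commits to no use of pre-kit opioid-use status, although the trial collects it anyway and its own script ties it to whether and when disposal is recorded. Starting from 86.4%, the effect of adjustment on power ranges from about nil (at most 0.4 points lost in the scenarios examined) to about 8 to 10 points gained. The trade is favorable because the possible loss is so small, but no particular gain can be promised.

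The conclusion rests on the absolute reading of the 20% change, independent patients, an assumed association, a between-arm contrast in all randomized participants, and day-4 answers that do not depend on arm. It would be wrong to infer that the primary comparison is invalid or underpowered without adjustment. The figures at 100 evaluable per arm illustrate attrition that the documents do not state.

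**What to change.** In section 9:

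1. Write the primary contrast as kit versus control among all randomized participants, in place of the baseline-versus-study-period wording. Say how participants who never reach the disposal question are counted.
2. State that the difference in disposal is adjusted for day-4 status in four levels that match the script: none taken (Q5 no); taken, none remaining (Q7 no); taken, pills remaining, planning to continue (Q8 yes); taken, pills remaining, not continuing (Q8 no). Add a missing category for incomplete day-4 answers. Fewer levels would not do: a split into none taken, continuing and not continuing leaves Q7-no patients unclassified, because they never see Q8.
3. Use a Cochran-Mantel-Haenszel test with a stratified risk difference, or a logistic model reported as a standardized risk difference so that the estimand remains a difference in rates. If a level may contain no reported disposals, as the script's routing allows, the stratified form is safer because the logistic estimate for that level would not be finite.
4. Keep the unadjusted comparison as supportive.
5. Reconcile sections 5.1 and 8.2 on allocation. If assignment is by calendar week, confirm that patients do not know their arm when they answer on day 4.

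The adjustment itself costs a few lines of text and slightly more analysis work. It needs no new questions, data or patients.

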## 1. Abstract

The majority of acute, short-term opioid tablets prescribed following surgery go unused. In a recent analysis of post-operative orthopedic and urologic surgery data at 7 days >60% of tablets were left unused, and patients reported no intention of using them, by post-operative day 7. Disposal of unused opioid medications is important to limit diversion, misuse, and conversion to new persistent use. These are salient to the patient and others around them including children, family and friends. Though patients can flush their unused opioids, early research has shown that providing patients with disposal techniques can improve proper disposal rates. In this proposal we seek to test, through a randomized clinical trial, if providing patients with an opioid disposal kit at key post-operative times can improve the rate of self-reported disposal as compared with usual care. Using an established, automated system our primary outcome will be self-reported opioid disposal rates. We will conduct a prospective RCT amongst patients undergoing urologic surgeries, neurosurgeries, and orthopedic surgeries.

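### The primary analysis is written as baseline versus study period and names no arm, contradicting the two-arm randomized design and its per-arm sample size

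*Supplement*

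**What the plan says.** Section 9 gives the primary analysis in a single sentence: "In our primary analyses, we will compare rates of opioid disposal (baseline vs. 6-week study period"). It states no arm, test, effect measure or analysis time point. The section mentions arms only for the comparison of sample characteristics. The significance rule follows: "All hypothesis tests will be two-sided using a two-sided alpha of 0.025 as our threshold for statistical" significance.

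The rest of the protocol sets up a comparison between arms:

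- Section 5.1: "This is a two-arm, randomized, controlled trial".
- Abstract, repeated in Background: the question is whether a kit "can improve the rate of self-reported disposal as compared with usual care".
- Section 3.1: "The primary outcome variable is rate of self-reported opioid disposal".
- Section 5.4: "We estimate that a sample size of 250 participants (125 per arm) will provide at least 80% power", at a two-sided alpha of 0.025, "to detect a 20% change in disposal rates". It adds: "Preliminary data suggest a baseline rate of 25" percent.

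That 25% is the only other mention of a baseline disposal rate. Under Section 8.2, messages go out on post-operative days 4, 7, 14, 21 and 28, and disposal is asked only of patients who report no further opioid use.

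**The concern.** The sentence that should state the randomized comparison describes a different one. Baseline could mean two things:

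- **The participant's status at day 4.** The contrast is then before versus after in the same people. If disposal is counted cumulatively, it can rise as patients recover and finish with their tablets, whether or not a kit arrives.
- **The 25% preliminary rate.** The contrast is then historical. The six-week study period contains both arms, so control patients are either pooled with kit recipients or left out.

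In neither case does the comparison isolate the kit. A rise over time, or a difference between periods, could be read as a kit effect, and a real effect could be misestimated. The document also leaves two incompatible primary contrasts open, so the choice could be made after the data are seen.

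**Working it through.** **1. The plan's own figure.** Inputs from 5.4: n = 125 per arm, control rate 25%, change of 20%, two-sided alpha 0.025 (z = 2.241). I read the change as absolute, 25% to 45%.

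Power = Φ[(|p2 − p1| − z·SE0)/SE1], with SE0 = √[2·p̄(1 − p̄)/n] and SE1 = √[(p1(1 − p1) + p2(1 − p2))/n].

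- p̄ = 0.35; SE0 = √(2 × 0.35 × 0.65/125) = 0.0603
- SE1 = √[(0.1875 + 0.2475)/125] = 0.0590
- Power = Φ[(0.20 − 2.241 × 0.0603)/0.0590] = Φ(1.098) = 86.4%

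This meets the stated 80% or more. A relative reading (25% to 30%) gives 8.7% and does not. The sample size therefore fits a test of kit against control.

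**2. Historical reading, arms pooled, true kit effect.** With control at 25% and kit at 45%, the pooled rate is (25% + 45%)/2 = 35%. Against 25%, the 20-point effect appears as 10 points.

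**3. Historical reading, inert kit.** Assumptions not in the documents: 25% is treated as a fixed value, and disposal in both arms is 5 or 10 points higher for reasons unrelated to the kit. With n = 250:

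- SE under 25% = √(0.25 × 0.75/250) = 0.0274; critical difference = 2.241 × 0.0274 = 0.0614
- Rise of 5 points: SE = √(0.30 × 0.70/250) = 0.0290; Φ[(0.05 − 0.0614)/0.0290] = Φ(−0.393) = 35%
- Rise of 10 points: SE = √(0.35 × 0.65/250) = 0.0302; Φ[(0.10 − 0.0614)/0.0302] = Φ(1.280) = 90%

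**4. Before/after reading, inert kit.** Assumptions not in the documents: 125 people, a final rate of 25%, a range of day-4 rates, and the two time points treated as independent samples. Using the formula in step 1:

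| Assumed day-4 rate | Final rate | Probability of rejection |
|---|---|---|
| 20% | 25% | 10% |
| 15% | 25% | 39% |
| 10% | 25% | 82% |
| 5% | 25% | 99% |

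Real day-4 and later answers would be paired. With cumulative disposal the two are positively correlated, so a paired test would tend to reject more often. The table shows direction and rough size, not the operating characteristics of a specified test.

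**The case against.** The strongest reply is that a between-arm test was plainly intended. The design, the objective and the per-arm sample size all point to it, and the stated power reproduces only as a contrast of 25% with 45% between two groups of 125. On this view the parenthesis is a slip. That is probably right about intent, and it makes the defect an internal contradiction rather than a settled plan to ignore randomization. It does not supply the missing statement, because no section shown specifies a between-arm primary test.

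A second reply is that the sentence may mean change from baseline compared between arms. This is not impossible: Section 5.1 lists disposal among the day-4 questions, and the kit is mailed only after day-4 consent. But the question reaches only patients reporting no further use, so there is no baseline for the full sample, and the sentence does not say this either.

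The illustrations can also be challenged. The documents give no day-4 rate and no drift, and the before/after result runs from 10% to 99% with the assumed start. It is also unclear whether disposal is asked again of everyone: the text-message script marks only patients planning further use for another message, while 8.2 describes questions at each time point. These objections stand against any single figure. They do not restore type I error control for the kit effect.

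**Conclusion.** The point holds as an internal contradiction that must be corrected. The only stated primary contrast names no arm, has no defined baseline and does not match the randomized question. Neither plausible meaning of baseline controls type I error for the kit effect. The pooled historical reading halves a true 20-point effect to 10 points. With an inert kit it rejects about 35% to 90% of the time if disposal drifts up by 5 to 10 points, against a nominal 2.5%. Those rejection rates rest on assumed drift and a fixed 25% comparator.

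A reader might infer that the trial is bound to be positive even with an inert kit, or that control patients play no part in the primary conclusion. The documents support neither. The rejection rate depends on rates they do not give, and on the pooled reading control patients are in the comparison, though mixed with kit recipients.

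**What to change.** Replace the primary-analysis sentence in Section 9 with one stating that:

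- the proportion reporting disposal by the last scheduled message (day 28) is compared between the kit and control arms, by assigned arm;
- the test is a two-proportion test at two-sided alpha 0.025, reported with the risk difference and its confidence interval;
- any comparison with baseline or with the preliminary rate is descriptive.

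The same paragraph should say how participants who are never asked about disposal, or who do not respond, are counted. Adjustment for surgical specialty is optional and is not needed to correct the contrast.

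The unit of assignment must also be reconciled. Section 5.1 assigns by alternating calendar week over six weeks, and Section 8.2 assigns individuals. A simple two-proportion test fits individual assignment. Under assignment by week (three weeks per arm) it would ignore clustering, so the test has to match whichever unit is confirmed.

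The cost is a paragraph of wording. Naming the arms leaves the total at 250, because the stated sample size already fits that comparison.
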